#### Community pharmacies and pharmacists.

##### Recruitment and selection

The recruitment process for community pharmacies will also follow top-down and bottom-up approaches to identify and recruit pharmacists. The research team will contact the General Council of Official Colleges of Pharmacists of Catalonia and the four Official Colleges of Pharmacists that exist in each of the four provinces of Catalonia to present the project. After the randomisation of the PC teams, each Official College of Pharmacists will be informed of the PC teams allocated to the intervention group; then, owners of community pharmacies that fulfil the inclusion criteria will be individually contacted and invited to participate in the study.

##### Inclusion criteria

Participating pharmacies have to fulfil the following criteria: a) it must be located within the area of the PC centres allocated to the intervention group, b) the pharmacy owner must be willing to participate and provide signed informed consent and c) if the pharmacy owner is not willing to participate, at least one other pharmacist who fulfils the inclusion criteria, must do so. To join the study, pharmacists have to a) sign an informed consent for participation in the clinical trial and the process evaluation, and b) attend the IMA intervention training.

#### Patients

##### Inclusion criteria

Patients will be identified from the electronic health records. All patients who a) are over 18 years old, b) receive a new prescription for lipid-lowering medication, antihypertensive medication, anti-platelet medication and/or antidiabetic medication (Table 1 shows the pharmacotherapeutic subgroups considered for study) from a participating GP during the seven-month study intervention period and c) do not refuse to participate in the study (see Ethics approval and consent to participate) will be included. A prescription is considered new if the patient has not had an active prescription from the same pharmacological group in the previous 6 months.

**Table 1 Tab1:** Pharmacotherapeutic groups considered for the IMA intervention, following the ATC Classification System [69]

**A10 - ****Drugs used in diabetes**	A10A - Insulins and analogues	*A10AB* - *Insulins and analogues for injection, fast-acting*
		*A10AC - Insulins and analogues for injection, intermediate-acting*
		*A10AD - Insulins and analogues for injection, intermediate- or long-acting combined with fast-acting*
		*A10AE - Insulins and analogues for injection, long-acting*
	A10B - Blood glucose lowering drugs, excluding insulins	*A10BA - Biguanides*
		*A10BB - Sulfonylureas*
		*A10BD - Combinations of oral blood glucose-lowering drugs*
		*A10BF - Alpha-glucosidase inhibitors*
		*A10BG - Thiazolidinediones*
		*A10BH - Dipeptidyl peptidase 4 (DPP-4) inhibitors*
		*A10BJ - Glucagon-like peptide-1 (GLP-1) analogues*
		*A10BK - Sodium-glucose co-transporter 2 (SGLT2) inhibitors*
		*A10BX - Other blood glucose-lowering drugs, excl. Insulins*
**B01 - ****Antithrombotic agents**	B01A - Antithrombotic agents	*B01AC - Platelet aggregation inhibitors excl. Heparin*
**C02 - ****Antihypertensives**	C02A - Antiadrenergic agents, centrally acting	
	C02C - Antiadrenergic agents, peripherally acting	
	C02D - Arteriolar smooth muscle, agents acting on	
	C02K - Other Antihypertensives	
**C03 - ****Diuretics**	C03A - Low-ceiling diuretics, thiazides	
	C03B - Low-ceiling diuretics, excl. Thiazides	
	C03C - High-ceiling diuretics	
	C03D - Potassium-sparing agents	
	C03E - Diuretics and potassium-sparing agents in combination	
	C03X - Other diuretics	
**C07 - ****Beta blocking agents**	C07A - Beta blocking agents	
	C07B - Beta blocking agents and thiazides	
	C07C - Beta blocking agents and other diuretics	
	C07D - Beta blocking agents, thiazides and other diuretics	
	C07F - Beta blocking agents, other combinations	
**C08 - Calcium channel blockers**	C08C - Selective calcium channel blockers with mainly vascular effects	
	C08D - Selective calcium channel blockers with direct cardiac effects	
	C08G - Calcium channel blockers and diuretics	
**C09 - ****Agents acting on the renin-angiotensin system**	C09A - ACE inhibitors, plain	
	C09B - ACE inhibitors, combinations	
	C09C - Angiotensin II receptor blockers (ARBS), plain	
	C09D - Angiotensin II receptor blockers (ARBS), combinations	
	C09X - Other agents acting on the renin-angiotensin system	
**C10 - ****Lipid modifying agents**	C10A - Lipid modifying agents, plain	*C10AA - HMG coa reductase inhibitors*
		*C10AB - Fibrates*
		*C10AC - Bile acid sequestrants*
		*C10AD - Nicotinic acid and derivatives*
		*C10AX - Other lipid modifying agents*
	C10B - Lipid modifying agents, combinations	*C10BA - Combinations of various lipid modifying agents*
		*C10BX - Lipid modifying agents in combination with other drugs*

Each new prescription of the listed pharmacotherapeutic groups (Table 1) will be considered the index prescription. A patient can be included as many times as a new prescription from the groups under study is issued.

### Randomisation

Paired PC teams included in the study will be randomised (1:1) into two parallel groups using a computerised random number generator. Concealment of allocation was guaranteed at the PC team level: PC teams will not be randomised until both teams in each pair agree to participate in the study. However, at the patient level, it is not possible to guarantee concealment of allocation due to the intrinsic characteristics of the study design by clusters.

### Blinding

Due to the nature of the intervention, healthcare professionals and patients cannot be blind to it.

### Intervention

The IMA intervention aims to promote SDM between patients and healthcare professionals by providing the latter with the knowledge, skills and tools to increase patients’ health literacy and thus help the patient make an informed decision.

In Spain, the prescription process is not standardised and there is no guarantee that the patient will be involved in the decision-making process. When GPs consider that a patient is eligible for CVD or diabetes treatment, they usually explain the health problem and the prescribed treatment to the patient. Each GP decides how to provide this explanation. In other situations, GPs can recommend the treatment and it is the nurse who explains the healthcare problem and treatment to the patient during a follow-up consultation. As part of follow-up, nurses promote medication adherence and explore any potential side effects of the newly prescribed treatment. During the process of drug dispensing, community pharmacists are expected to explore patients’ knowledge and doubts about the medication, although this practice is not standardised either.

The foundations of the IMA intervention are SDM and the harmonisation and standardisation of clinical practice among healthcare professionals. GPs will be trained to use SDM during the time of consultation by informing the patient about their disease and the available treatment options with the help of decision aids (leaflets), and exploring their perspectives and queries before recommending a new pharmacological treatment, following the principles of the SDM model by Elwyn et al. [70, 71]. Finally, nurses and pharmacists will be encouraged to explore patients’ queries and use the decision aids to help standardise the discourse and improve collaboration among healthcare professionals.

As part of the implementation strategy of the IMA intervention, there are three inputs which are essential to achieve the intervention outcomes. First, top-down and bottom-up recruitment approaches are taken to increase professional engagement. Second, after the randomisation of the PC teams, healthcare professionals from the intervention group receive training on the IMA intervention, lasting 6 h. The training covers several aspects of non-initiation and other topics such as communication skills, health literacy and SDM. And lastly, decision aids have been designed to support the IMA intervention. These include one leaflet for each of the five pharmacotherapeutic groups and an *ad-hoc* website (available at: www.iniciadores.es). The leaflets will homogenise the intervention and provide tools to transmit the concepts of risk and benefit of the disease, treatment and alternatives. The leaflets contain a link to the website with a quick response code and this is considered a reliable source of information on CVD and diabetes. A full description of the intervention and its implementation strategy are described elsewhere [53].

Healthcare professionals in the control group will not receive training on SDM nor access to the decision aids and will be asked to provide usual care.

All participating professionals will receive a reinforcement session on the registry of clinical outcomes in the e-health records system and IMA-cRCT ethical standards.

PC team pairs will be randomised to the intervention and control groups and training sessions will be scheduled. Upon completion of training, each pair of PC teams will start the 7-month intervention in March 2022. The study period will last 7 months to account for healthcare professionals’ summer holidays, which last up to a month. During this time, the intervention will be applied to each patient meeting inclusion criteria. Figure 2 shows the trial flow-chart based on CONSORT guidelines.

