### Data collection

The SIDIAP database will be used to collect data for the evaluation of the effectiveness and cost-effectiveness of the IMA intervention. It implies the absence of any *ad-hoc* registry for the sake of the RCT.

SIDIAP gathers information from the electronic medical records of all patients seen by the public PC provider since 2010. This database provides information on patients’ sociodemographic and clinical data, including visits to primary care, health problems, sick leave periods, prescribed medicines, immunisations, laboratory results, clinical outcomes, and information on dispensed medication in any Catalan pharmacy [73]. All these records are dated.

The SIDIAP database is an encrypted, anonymised, secure database. It is managed by the Catalan Health Institute and CatSalut and provides real-world health data generated by the public health system in Catalonia to the scientific community under the legal and regulatory framework, following ethical principles, and maintaining transparency concerning the public program [74].

The SIDIAP database will be used to identify all patients that fulfil inclusion criteria to define the cohort of patients. They will be identified based on GP prescriptions. All variables will be collected for this cohort. All patient-related outcomes will be obtained from the encrypted and anonymised RWD databases. Patients’ personal information will not be provided to the research team. For each patient, data will be collected for the 12 months before the index prescription (for adjustment purposes) and from the subsequent 12 months (follow-up). Figure 3 depicts the observation periods in which the intervention is applied to patients. Information on healthcare professionals will be gathered through questionnaires at the training sessions [53].

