#### Effectiveness outcomes

##### Primary outcome measures

*Initiation*: Patients who receive a new prescription will be considered initiators if they obtain their prescriptions in a community pharmacy during the following month [6]. Sensitivity analysis will be performed for a follow-up period of 3 months. Prescription and dispensation databases from SIDIAP will be compared to classify prescriptions as initiated and non-initiated.

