### Sample size

According to previous results, the proportion of non-initiation of medications for CVD and diabetes in Catalonia is between 8–13% [18]. For sample size calculations, a proportion of 10% has been assumed. The sample size was estimated based on calculations for cluster randomised controlled trials [79]. Assuming a reduction in the incidence of non-initiation of 3%, a power of 80% and a significance level of 5%, given that the intracluster correlation coefficient for PC teams is 0.01, and assuming that, on average, each GP issues 30 new prescriptions of the selected medicines in 6 months, accounting for 10% of losses (due to incompleteness of data in clinical records), the necessary sample is 3,878 prescriptions and 130 GPs.

Considering 80% of urban PC centres in Catalonia and assuming a minimum number of five GPs per urban PC team and 2 per rural PC team, we will contact twenty-four PC teams to invite them to participate; fourteen from urban areas and ten from rural areas. PC teams will be included until the sample size is reached, i.e., 65 GPs are included in both the control and intervention groups.

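### The intervention can change who is prescribed, and so who is counted, and no analysis described in the article separates fewer unfilled prescriptions from more patients starting treatment

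*Protocol article*

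**What the plan says.** Entry. Under Patients, Inclusion criteria, adults join if they "receive a new prescription for lipid-lowering medication, antihypertensive medication, anti-platelet medication and/or antidiabetic medication" from a participating GP in the seven-month intervention period. Data collection says of the cohort: "They will be identified based on GP prescriptions".

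Outcome. Under Primary outcome measures: "Patients who receive a new prescription will be considered initiators if they obtain their prescriptions in a community pharmacy during the following month". The denominator is therefore issued prescriptions.

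Timing. The Intervention section has GPs inform patients about the disease and the options, "exploring their perspectives and queries before recommending a new pharmacological treatment", with leaflets that also cover alternatives to the drug. Training follows randomisation. Blinding says that professionals and patients cannot be blinded, and Randomisation concedes that concealment cannot be guaranteed at patient level.

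Analysis. Statistical analysis restricts the intention-to-treat set to patients who meet the inclusion criteria. It adjusts for recorded patient characteristics that predict non-initiation and differ at baseline. The sensitivity analyses under Effectiveness vary GP training attendance, GP completion, imputation and covariate adjustment. None changes the denominator, and no comparison of prescribing volume between arms is described.

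**The concern.** The conversation that defines the GP component happens before the event that makes a patient eligible. A reluctant patient in the intervention arm may be persuaded and fill the prescription, which is a gain in treatment. The same patient may instead decline, receive no prescription and never enter the cohort. In usual care, where the article says that patient involvement is not guaranteed, that patient may be prescribed and counted as a non-initiator.

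The article's own theory makes this plausible. Its Background lists fear of adverse effects, doubts about effectiveness, pill burden and a preference for lifestyle measures among the reasons for non-initiation, and a conversation before prescribing would bring these out.

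What is at stake is interpretation. A lower non-initiation share could mean that more patients start treatment, that fewer prescriptions go to patients who would not have filled them, or both. Secondary adherence, cardiovascular risk, events and costs are analysed in the same cohort, so their arm comparisons share the problem; its direction and size there have not been worked out.

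**Working it through.** **Inputs from Sample size.** Control non-initiation: "For sample size calculations, a proportion of 10% has been assumed", from a source range of 8–13%. Planned reduction 3%, power 80%, significance level 5%, intracluster correlation 0.01, 30 prescriptions per GP, 10% losses. The result is given as 3,878 prescriptions and 130 GPs.

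**Reproducing the plan's figure.** Read the 3% as absolute (10% to 7%) and the test as two-sided.
- Per arm, unpooled variance: (1.960 + 0.842)² × (0.10×0.90 + 0.07×0.93) / 0.03² = 1,352.6.
- Design effect: 1 + (30 − 1) × 0.01 = 1.29.
- Total: 2 × 1,352.6 × 1.29 / 0.90 = 3,877.5, i.e. 3,878.
- GPs: 3,878 / 30 = 129.3, i.e. 130.

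The stated size reproduces exactly. The sample-size arithmetic is not at fault, and the target is confirmed as 10% to 7%.

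**Selection, worst case.** Assumption, not from the article: a fraction x of would-be prescriptions is not issued in the intervention arm, and all of them would have gone unfilled. Observed non-initiation is then (0.10 − x)/(1 − x).
- x = 1%: 0.09/0.99 = 9.1%.
- x = 2%: 0.08/0.98 = 8.2%.
- Setting the result to 7%: x = 0.03/0.93 = 3.23%. That is 0.97 of 30 prescriptions per GP, about 63 of 1,939 per arm, or 32% of would-be non-initiators (3.23/10).

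At x = 3.23% there are 900 initiators per 1,000 candidates in both arms, yet the primary comparison shows the whole planned effect. With the slightly smaller intervention arm, power to declare that difference is still about 79%. Across the 8–13% base range, a 3-point fall needs x = 0.03/0.95 = 3.2% to 0.03/0.90 = 3.3%.

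**Selection, mixed case.** Let a share s of the withheld prescriptions come from would-be non-initiators. Solving (0.10 − s·w)/(1 − w) = 0.07 gives w = 0.03/(s − 0.07).

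| s | withheld, w | initiators per 1,000 candidates |
|---|---|---|
| 100% | 3.2% | 900 |
| 75% | 4.4% | 889 |
| 50% | 7.0% | 865 |

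In the last two rows the primary outcome reads 7% while fewer candidates start treatment than under usual care (900).

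**The case against.** The strongest reply is that a denominator of prescriptions is what the trial set out to use. Study aims speaks of improving initiation in patients who have already been prescribed a treatment, and the Background defines initiation relative to a prescribed medication. If shared decision-making spares patients prescriptions that they do not want, fewer unfilled prescriptions is a legitimate result. This stands. It means that the outcome is not wrong in itself; what remains open is whether a lower share also means more people treated.

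Second, only the GP consultation precedes the prescription. Nurse follow-up and the pharmacist's discussion can act at or after it. This also stands: part of any effect can arise after entry, where this selection does not operate.

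Third, the baseline comparison and covariate adjustment offer some protection. They can reveal selection on recorded characteristics, but intention to fill is not recorded, so the protection is partial.

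Fourth, this is a condensed article, and supportive analyses may sit in a full plan that is not shown. That is fair as to analyses. But the article itself fixes the entry rule, the denominator and the timing of the GP component, and Strengths and limitations does not mention the selection that these create.

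**Conclusion.** The concern holds as a problem of interpretation. Entry and the primary denominator come after randomisation and after the GP component has acted, and nothing described in the article separates more treatment from fewer prescriptions. A small shift in prescribing would be enough to matter: about one prescription in 30 per GP in the worst case.

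A reader might infer that the planned 3-point fall would be an artefact, or that it is likely to appear with no extra patient treated. The documents do not support that. They give no figure for how shared decision-making changes prescribing. The 3.2% result rests on the assumption that every withheld prescription would have gone unfilled, which is the extreme case. The figures are scenarios, not an estimate of bias.

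A reader might also want to allow a claim of improved initiation only if initiated treatments per assigned patient are not lower in the intervention arm. That rule would work badly. It passes the case of 900 initiators in both arms. It would also often fail a true effect. With 1,939 prescriptions per arm, moving from 10% to 7% raises the initiated rate by 0.93/0.90, a log ratio of 0.033. Its Poisson standard error is √(1/1,803 + 1/1,745) = 0.034, so the estimate falls below no difference about 16% of the time before any variation between teams.

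**What to change.** Keep the primary outcome. Pre-specify two supportive comparisons by arm from SIDIAP. The denominator is the patients assigned to each participating GP before randomisation, and the same GPs' preceding year serves as baseline:

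1. new study-drug prescriptions per 1,000 assigned patients;
2. initiated new treatments per 1,000 assigned patients.

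Report each with a confidence interval adjusted for clustering, and attach no pass/fail rule. Describe a lower non-initiation share as fewer prescriptions left unfilled. Describe it as more patients starting treatment only where the two rates support that reading. Add the selection mechanism to Strengths and limitations.

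The cost is one extra extraction (list sizes, prescription counts and dispensing per GP) and two models. Data collection says that SIDIAP already holds prescribing and dispensing records; that it can also supply each GP's assigned list at a fixed date is assumed here. The drawback is that list-based rates are noisier than the per-prescription share, so they inform interpretation and do not replace the primary test.

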**Fig. 2 Fig2:**
[figure not shown]
CONSORT flow diagram [72]

### Data collection

The SIDIAP database will be used to collect data for the evaluation of the effectiveness and cost-effectiveness of the IMA intervention. It implies the absence of any *ad-hoc* registry for the sake of the RCT.

SIDIAP gathers information from the electronic medical records of all patients seen by the public PC provider since 2010. This database provides information on patients’ sociodemographic and clinical data, including visits to primary care, health problems, sick leave periods, prescribed medicines, immunisations, laboratory results, clinical outcomes, and information on dispensed medication in any Catalan pharmacy [73]. All these records are dated.

The SIDIAP database is an encrypted, anonymised, secure database. It is managed by the Catalan Health Institute and CatSalut and provides real-world health data generated by the public health system in Catalonia to the scientific community under the legal and regulatory framework, following ethical principles, and maintaining transparency concerning the public program [74].

The SIDIAP database will be used to identify all patients that fulfil inclusion criteria to define the cohort of patients. They will be identified based on GP prescriptions. All variables will be collected for this cohort. All patient-related outcomes will be obtained from the encrypted and anonymised RWD databases. Patients’ personal information will not be provided to the research team. For each patient, data will be collected for the 12 months before the index prescription (for adjustment purposes) and from the subsequent 12 months (follow-up). Figure 3 depicts the observation periods in which the intervention is applied to patients. Information on healthcare professionals will be gathered through questionnaires at the training sessions [53].

**Fig. 3 Fig3:**
[figure not shown]
SPIRIT [55] figure

**Table 2 Tab2:** Events related to CVD and diabetes considered in measuring the effectiveness of the IMA intervention, as described in the 10th revision of the International Statistical Classification of Diseases and Related Health Problems (ICD-10) [69]

**E00-E90 - Endocrine, nutritional, and metabolic diseases**	E10-E14 - Diabetes mellitus	*E10 - Type 1 diabetes mellitus*
		*E11 - Type 2 diabetes mellitus*
		*E12 - Malnutrition-related diabetes mellitus*
		*E13 - Other specified diabetes mellitus*
		*E14 - Unspecified diabetes mellitus*
	E70-E90 - Metabolic disorders	*E78 - Disorders of lipoprotein metabolism and other lipidaemias*
**I00-I99 - Diseases of the circulatory system **	I10-I15 - Hypertensive diseases	*I10 - Essential (primary) hypertension*
		*I11 - Hypertensive heart disease*
		*I12 - Hypertensive renal disease*
		*I13 - Hypertensive heart and renal disease*
	I20-I25 - Ischaemic heart diseases	*I20 - Angina pectoris*
		*I21 - Acute myocardial infarction*
		*I22 - Subsequent myocardial infarction*
		*I23 - Certain current complications following acute myocardial infarction*
		*I24 - Other acute ischaemic heart diseases*
		*I24 - Chronic ischaemic heart disease*
	I30-I52 - Other forms of heart disease	*I50 - Heart failure*
		*I51 - Complications and ill-defined descriptions of heart disease*
	I60-I69 - Cerebrovascular diseases	*I60 - Subarachnoid haemorrhage*
		*I61 - Intracerebral haemorrhage*
		*I62 - Other nontraumatic intracranial haemorrhages*
		*I63 - Cerebral infarction*
		*I64 - Stroke, not specified as haemorrhage or infarction*
		*I65 - Occlusion and stenosis of precerebral arteries, not resulting in cerebral infarction*
		*I66 - Occlusion and stenosis of cerebral arteries, not resulting in cerebral infarction*
		*I67 - Other cerebrovascular diseases*
		*I68 - Cerebrovascular disorders in diseases classified elsewhere*
		*I69 - Sequelae of cerebrovascular disease*
	I70-I79 - Diseases of arteries, arterioles, and capillaries	*I70 - Atherosclerosis*
		*I71 - Aortic aneurysm and dissection*
		*I72 - Other aneurysm and dissection*
		*I73 - Other peripheral vascular diseases*
		*I74 - Arterial embolism and thrombosis*
		*I77 - Other disorders of arteries and arterioles*
		*I78 - Diseases of capillaries*
		*I79 - Disorders of arteries, arterioles and capillaries in diseases classified elsewhere*
**N00-N99 - Diseases of the genitourinary system**	N00-N08 - Glomerular diseases	*N06 - Isolated proteinuria with specified morphological lesion*
		*N08 - Glomerular disorders in diseases classified elsewhere*
	N17-N19 - Renal failure	*N17 - Acute renal failure*
		*N18 - Chronic kidney disease*
		*N19 - Unspecified kidney failure*

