##### Other outcome measures

These data will be collected from the SIDIAP database for the 12 months after the index prescription.*Clinical parameters:* Clinical parameters assessed will depend on the diagnosis. Patients with type II diabetes: glycated haemoglobin, glomerular filtration rate, impaired fasting glucose; with dyslipidaemia: high-density lipoprotein, low-density lipoprotein and total cholesterol; and with hypertension: systolic and diastolic blood pressure.*Cardiovascular events:* Events related to CVD and diabetes, categorised according to the International Classification of Diseases, 10th version (ICD10). Table 2 shows the list of events considered.

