#### Economic model

Economic models allow extrapolation of the cRCT’s results to evaluate the long-term cost-effectiveness of interventions assessed in short trials [90].

The model will be used to estimate long-term cost-effectiveness and cost-utility based on increased lifetime costs and effects for patients who receive the IMA intervention compared to those who receive usual care. The ICER of the IMA intervention in comparison to usual care will be reported in terms of cost per LYG, and the incremental cost-utility ratio (ICUR) in terms of cost per QALY gained from the IMA intervention.

The model will track patients included in the IMA-cRCT through CVR, any CVD-related events (Table 2) and death. It will contain estimates of average annual care costs and average utilities (quality of life) for each disease state, which will be accrued over 1-year cycle lengths until all patients enter the absorbing state of death (lifetime horizon, as is recommended for chronic conditions [91, 92]).

For the first year, information on transition probabilities will be obtained from the IMA-cRCT study. After the first year, information on transition probabilities will be obtained from RWD from the SIDIAP database and the existing literature. Yearly transitions will be incorporated into the model, which will consider adherence as a dynamic process. The economic model will be designed according to an ongoing epidemiological cohort study and based on previously published models [93, 94].

An annual discount rate of 3% for both costs and effects for the period of the main analysis beyond 12 months [95] will be applied.

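### Table 2 counts the index conditions (diabetes E10-E14, dyslipidaemia E78, hypertension I10) as cardiovascular events, and its ischaemic heart disease block lists I24 twice and no I25

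*Protocol article*

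**What the plan says.** Under Other outcome measures, cardiovascular events are those related to CVD and diabetes, grouped by ICD-10 and collected for the 12 months after the index prescription. The section adds: "Table 2 shows the list of events considered". Table 2 is titled "Events related to CVD and diabetes considered in measuring the effectiveness of the IMA intervention". Its lines include:

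- "E11 - Type 2 diabetes mellitus", with the rest of E10-E14
- "E78 - Disorders of lipoprotein metabolism and other lipidaemias"
- "I10 - Essential (primary) hypertension"
- in block I20-I25, I24 for other acute ischaemic heart diseases and then "I24 - Chronic ischaemic heart disease", with no I25 line

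Patients enter if they "receive a new prescription for lipid-lowering medication, antihypertensive medication, anti-platelet medication and/or antidiabetic medication" from a participating GP (Patients, Inclusion criteria).

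The Economic model section follows patients through cardiovascular risk, "any CVD-related events (Table 2) and death". It takes first-year transition probabilities from the trial.

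**The concern.** An outcome event should be something that can happen to the patient after entry and that the intervention might prevent. Hypertension, diabetes and dyslipidaemia are, for most participants, the reason the index drug was prescribed. The article recognises this elsewhere. Other outcome measures chooses the clinical parameters according to whether the patient has type II diabetes, dyslipidaemia or hypertension, and Sociodemographic variables and diagnostics collects diagnoses at baseline as patient characteristics. Table 2 then lists the same conditions as events.

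A patient whose hypertension is first coded at the visit that produced the first antihypertensive prescription, or at a later one, would be counted as having an event. Two results are at stake: the trial's comparison of cardiovascular events, and any first-year model transitions estimated from the same list. The I24 line is a separate error in the same table: an extraction that follows the printed codes would not request I25.

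**Working it through.** **Entry criteria against event list**

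| Drug class that defines entry | Usual indication | Listed in Table 2 as an event? |
|---|---|---|
| Antihypertensive | Hypertension | Yes, I10 |
| Lipid-lowering | Dyslipidaemia | Yes, E78 |
| Antidiabetic | Diabetes | Yes, E10-E14 |
| Antiplatelet | Vascular disease | Some vascular codes could be the indication |

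For three of the four classes, the usual indication is on the list. No section restricts the outcome to new or acute codes or sets the indication aside.

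**Figures in the plan.** The article gives no event rate, power or sample size for this outcome. Its sample size is for initiation and can be reproduced. For 10% v 7%, two-sided 5%, 80% power and unpooled variance, n = 1,352.6 per arm. Then 2 × 1,352.6 × 1.29 / 0.9 = 3,877.5, which rounds up to the stated 3,878. The design effect is 1 + (30 − 1) × 0.01 = 1.29. No input comes from Table 2, so the sample size is untouched.

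**Illustration of dilution if codes are pooled.** All rates here are assumptions, since the document gives none. Let e be the 12-month risk of a true event and c the share of patients with an index-condition code counted in the window. Take c as equal in both arms and independent of true events. The pooled risk is C = 1 − (1 − c)(1 − e). The share of counted control patients who have only an index diagnosis is c(1 − e)/C. With e = 3% (control) v 2.25% (intervention), the true risk ratio is 0.75:

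| c | C, control | C, intervention | Risk ratio | Index diagnosis only (control) |
|---|---|---|---|---|
| 0% | 3.0% | 2.25% | 0.75 | 0% |
| 10% | 12.7% | 12.0% | 0.947 | 76% |
| 30% | 32.1% | 31.6% | 0.984 | 91% |
| 50% | 51.5% | 51.1% | 0.993 | 94% |

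For c = 10%: control 1 − 0.90 × 0.97 = 0.127; intervention 1 − 0.90 × 0.9775 = 0.12025; ratio 0.947; share 0.10 × 0.97 / 0.127 = 0.76.

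A second set of assumptions, with true risk ratio 0.80 and control event risk 1% to 5%, gives:

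- c = 5%: pooled ratio 0.90 to 0.97; 49% to 83% index diagnosis only
- c = 20%: pooled ratio 0.97 to 0.99; 79% to 95% index diagnosis only

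Under these assumptions any c above zero pulls the ratio towards 1. How far depends on c and e, which the document does not supply.

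**If events are reported by category.** Infarction and stroke are then not diluted. The E10-E14, E78 and I10 categories would still be presented as effectiveness events while containing mainly entry diagnoses for patients on the matching drug.

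**Economic model.** The model wording mentions CVD-related events, whereas the Table 2 title covers CVD and diabetes, so the diabetes and lipid codes might be read as excluded. I10 would remain on that reading, because Table 2 places it among diseases of the circulatory system.

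**The case against.** **Composite.** No section defines an outcome of any Table 2 code. Events are said to be grouped by ICD-10, and the Effectiveness section gives no model for them. This stands: dilution is conditional on pooling. It does not make a diagnosis of the index condition an event.

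**Detail left to the SAP.** Incident-code and look-back rules commonly sit in a SAP, and the article already plans dated records and 12 months of pre-index data. This stands in part. The missing rule is not the finding; the printed list is. An incident-only rule would also not cure it, because a first I10, E11 or E78 code can be entered with or soon after the first prescription.

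**Stronger readings.** A reader might infer that the outcome largely measures index diagnoses. That depends on the unknown c, and at c = 0 there is no dilution. A reader might also infer that coding differs by arm because intervention GPs discuss the disease more. The article does not show this, and the Intervention section gives professionals in both arms a session on recording clinical outcomes. Nor does it show that the transition probabilities will be wrong: the model also draws on an ongoing cohort study and published models.

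**Risk of over-correction.** Requiring every code to be absent in the previous 12 months would discard true recurrences, such as a second stroke. Deleting the diabetes codes outright would lose new diabetes in a patient who entered on an antihypertensive. Both points stand and shape the fix. Chronic vascular codes can themselves be indications, so a small overlap remains even after correction.

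**Importance and the I24 line.** This is an outcome below the primary and secondary ones. The I24 line is a slip whose intent the label and block heading suggest, and omission at extraction is a risk, not a certainty.

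**Conclusion.** The concern holds as a wrongly fixed code list. Following Table 2 as printed, the index condition can count as an event in the cardiovascular-event outcome and, at least for I10, in the model. The size of any distortion cannot be derived from the document. The ratios of 0.95 and 0.99 rest on assumed event risks, an assumed coding share equal in both arms, independence and pooling. The duplicated I24 with no I25 is a definite error in the list.

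The reach is limited. Initiation, secondary adherence, cardiovascular risk, the sample size and the trial-based cost-effectiveness ratio do not use Table 2. The correction is worth making because it is cheap before extraction and because the list is also meant to feed a lifetime model.

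**What to change.** 1. Remove E10-E14, E78 and I10 from the event list for effectiveness and for model transitions, and keep them as baseline diagnoses. Newly recorded diabetes, hypertension or dyslipidaemia that is not the index indication may be reported separately.
2. For chronic codes (for example chronic ischaemic heart disease, I50, I70, N18), count only a first record after the index date with no earlier record.
3. For acute codes (for example I21, I22, I60-I64, N17), count any new dated episode after the index date, including recurrences.
4. Correct the second I24 line to the code intended within I20-I25.
5. Make the Economic model section refer to the corrected list.

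The cost is an edit to the code list and extraction rule before the database request, and fewer counted events. Twelve months of pre-index data are already planned. A longer look-back for chronic codes would need earlier diagnosis dates in the request; the Data collection section says the database holds records since 2010.
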